### Study design

2.1

In the first phase, we focus on developing a multimodal data-driven intelligent system for exercise prescription. To achieve this, we will initially recruit 1,000 participants for AI model training and testing. Of these, 80% (800 participants) form the training set. To enhance the robustness and generalizability of the AI model, we will use ChatGPT to simulate an additional 9,200 cases based on the initial 800, resulting in a comprehensive training set of 10,000 instances. The remaining 20% (200 participants) will be reserved as a testing set. This diverse dataset will then be annotated by a team of 10 experienced doctors from the Department of Mental Health at Guangdong Second Provincial General Hospital. Their expertise will ensures the accuracy and clinical relevance of the data labeling, which is critical for the development of a reliable and effective AI system.

In our analysis, we will set the effect size at 0.5 to assess the intervention’s effectiveness. This value represents a medium effect size, which is considered substantial in the context of our study. Following the development and preliminary testing of the AI model, the second phase of the study will involves an RCT with 50 participants. These participants are randomly divided into two groups: 25 in the experimental group and 25 in the control group. The experimental group will receives personalized exercise prescriptions generated by the newly developed AI system, while the control group will receives standard exercise recommendations. This phase aims to evaluate the efficacy of the AI-driven exercise prescription system in a real-world clinical setting. The RCT’s design ensures that the results are robust and can be attributed specifically to the intervention, thereby providing strong evidence of the system’s potential benefits for individuals with mental illnesses.

The effectiveness of the AI-driven exercise prescriptions is evaluated at multiple time points: initially at the end of the 6 months trial period (Trial Completion Assessment), followed by a 6 months follow-up assessment and a 12 months follow-up assessment. These assessments are designed to track and compare the short-term and long-term impacts of the AI-driven exercise prescriptions on the mental health outcomes of the participants (shown in Figure 1).

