### Recruitment

2.2

Participants for the study will be recruited from the general community and the Department of Mental Health at Guangdong Second Provincial General Hospital, utilizing platforms like WeChat or other social media to effectively reach and engage potential participants. To reach a diverse pool of potential participants, advertisements will be placed in community centers and local newspapers in Guangzhou. At the Department of Mental Health, individuals receiving care will have the opportunity to consent to the use of their medical records for research purposes and express their interest in participating in research studies. Prospective participants will initially undergo a telephone screening process to determine their eligibility. This screening will include an evaluation based on predefined inclusion and exclusion criteria, alongside the Physical Activity Readiness Questionnaire for Everyone (PAR-Q Plus) (29), a widely recognized tool for assessing an individual’s readiness for physical exercise. Upon passing the initial screening, eligible participants will be invited to a detailed consent and screening session. This session, which can be conducted either over the phone or in person, will provide comprehensive information about the study, including its objectives, methodology, potential risks, and benefits. During this session, research staff will ensure that participants fully understand the study and are comfortable with their involvement, thereby upholding the highest standards of ethical research practice. For participants involved in the AI part of data collection, we are offering a subsidy of 100 RMB per person. This incentive is designed to encourage their active participation and consistent engagement with the data collection process. Additionally, for participants in the RCT, we are providing a more substantial subsidy of 300 RMB per person.

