### RCT design and methods

4.1

Our study employs a parallel-group RCT to evaluate the effectiveness of an AI-based exercise prescription system in mental health management. Participants are divided into two groups: an intervention group and a control group, each consisting of 25 individuals. This balanced design allows for a robust comparison of outcomes between the groups, thereby providing reliable evidence on the impact of the AI-driven intervention. The randomization process involves a computer-generated sequence, ensuring an unbiased assignment of participants into the intervention group (*n* = 25) and the control group (*n* = 25). Stratification is conducted based on key variables such as age, gender, and specific mental health diagnoses to maintain comparable groups. This methodology is critical for mitigating potential confounding factors and ensuring the validity of the study results. In the intervention group, each participant receives a personalized exercise prescription tailored by the AI system, based on their unique health profile. This approach aims to maximize the efficacy of the exercise regimen in improving mental health outcomes. The control group, on the other hand, receives standard care practices, which may include general health advice or standard exercise recommendations. The distinction in treatment between the groups is central to evaluating the added value of the AI-driven exercise prescriptions.

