### Intervention measures

4.2

The 25 participants in the intervention group receive personalized exercise prescriptions generated by our AI model. These prescriptions are meticulously tailored based on each participant’s health profile and mental health status. The AI model determines the most suitable Type of Exercise for each individual, ranging from aerobic activities to strength training, depending on their physical and mental health needs. The Frequency of exercise is set, aiming for a balance that maximizes benefit while considering each individual’s lifestyle and capacity. Intensity levels are also customized, ensuring that exercises are challenging yet safe and achievable for each participant. Lastly, the Duration of each exercise session is specified by the AI model, optimizing the time spent on each activity for maximum efficacy. For example, for a participant with moderate depression and a sedentary lifestyle, the AI model might prescribe light aerobic activities like brisk walking or cycling for 30 min, three times a week. The intensity would be set at a moderate level, ensuring the participant can comfortably sustain the activity while gaining mental health benefits. The model may also suggest gentle yoga twice a week to improve flexibility and reduce stress, tailoring the duration to 20 min per session to match the participant’s initial physical fitness level. The intervention lasts for a period of 4 weeks, during which participants adhere to their personalized exercise regimen. The control group, comprising another set of 25 participants, receives standard care practices. This generally includes generic health advice and non-tailored exercise recommendations, reflecting the conventional approach to mental health management. The control group’s treatment does not involve the AI-driven customization of exercise parameters, serving as a baseline to evaluate the effectiveness of the personalized exercise prescriptions provided to the intervention group.

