Moreover, the enhanced efficacy of these personalized exercise regimes could lead to better mental health outcomes. Regular, tailored physical activity can positively impact various aspects of mental health, including mood elevation, reduction in anxiety symptoms, and overall improvement in mental well-being. This suggests that personalized exercise prescriptions, as adjuncts to conventional mental health treatments like psychotherapy and medication, could offer a comprehensive approach to mental health care.

While our research has yielded encouraging outcomes, it is not without limitations. The complexity of mental health disorders and the variability in individual responses to exercise highlight the challenges in developing universally effective AI-driven interventions. Additionally, the reliance on self-reported data in some of our assessments could introduce bias or inaccuracies. Future research should aim to incorporate more objective measures and explore the long-term sustainability of AI-prescribed exercise regimes.

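### The design cannot ensure attribution specifically to the intervention for self-rated outcomes, because participants can readily infer their arm

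*Protocol article*

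**What the plan says.** Section 2.1 (Study design) states that the trial's "design ensures that the results are robust and can be attributed specifically to the intervention", and goes on to call the result strong evidence of benefit.

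The arms are described in 4.1 and 4.2. In the intervention group "each participant receives a personalized exercise prescription tailored by the AI system", covering type, frequency, intensity and duration. Of the control group's care, 4.2 says: "This generally includes generic health advice and non-tailored exercise recommendations". Section 4.1 is looser and describes standard care "which may include general health advice or standard exercise recommendations". No sham plan or plan of matched format is described.

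Before entry, a consent session "will provide comprehensive information about the study, including its objectives, methodology, potential risks, and benefits" (2.2 Recruitment).

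On protection against bias, 4.1 says: "The randomization process involves a computer-generated sequence". It adds stratification by age, gender and diagnosis. The article does not mention blinding of participants, testers or analysts.

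Section 4.3 and Table 2 list the State and Trait Anxiety Inventory (STAI), the Pittsburgh Sleep Quality Index (PSQI) and health-related quality of life, together with cognitive and physical performance tests. The Discussion concedes that "the reliance on self-reported data in some of our assessments could introduce bias or inaccuracies".

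**The concern.** The sentence in 2.1 is an affirmative claim about what the design guarantees, so it can be tested against the design in the same article. Random allocation makes the groups comparable at the start. It does nothing about what happens once people recognise which kind of care they have been given and are then asked how they feel.

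The stated aim is better mental health outcomes. The only psychiatric symptom scale in Table 2 is the STAI, which participants complete themselves. The depression scale appears only among the model inputs in Table 1. The outcomes that bear most directly on the claim are therefore those most exposed to expectation: hope in people given an AI-tailored plan, disappointment in people given generic advice. Both plausibly push the comparison towards the AI arm. A difference on these scales could be reported as an effect of the prescription when part or all of it is not.

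The Discussion's caveat treats self-report as a general accuracy limit. It does not connect it to knowledge of the arm, and it does not withdraw the assurance in 2.1.

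**Working it through.** The article gives no figure for this bias, so there is nothing to reproduce. The check is a reading of the sections against each other, followed by an illustration of size.

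**Step 1: can participants recognise their arm?** Sections 4.1 and 4.2 give one arm a plan with four individual parameters and the other untailored advice. Section 2.2 has everyone told the objectives and methodology beforehand. Someone who knows that the study concerns AI-personalized prescriptions, and who then receives either such a plan or general advice, can readily infer the arm.

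**Step 2: which outcomes depend on that knowledge?** Table 2 has 13 rows. By the nature of the instruments:
- about 6 are self-report: IADL; subjective memory complaints; the reproductive, cognitive activity and physical activity questionnaires; the row with PSQI and life space; STAI; quality of life and sedentary behavior;
- 6 are staff-administered: MoCA and MMSE; the row with Rey-O and line orientation; physical performance; Short Physical Performance Battery (SPPB); 400 m walk; 30 s sit-to-stand;
- 1 (Descriptors) is unclear.

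**Step 3: does anything in the design remove the bias?** Section 4.1 relies on the random sequence and stratification. Both act on baseline differences. Neither acts on reporting after allocation.

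**Step 4: is the contrast confined to AI tailoring?** Section 4.1 leaves open that some controls receive general health advice with no exercise recommendation. A difference could then reflect having an exercise plan at all, which further weakens the word *specifically*.

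**Step 5: illustration of size.** Inputs: 25 per arm (2.1, 4.1) and two-sided 0.05 (4.5). Assumptions: zero true effect, a bias of b in SD units, and a normal approximation.

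SE = √(2/25) = 0.283

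P(significant) = 1 − Φ(1.96 − b/SE) + Φ(−1.96 − b/SE)

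| Assumed b (SD) | b/SE | P(significant) | b as share of the 0.5 effect size in 2.1 |
|---|---|---|---|
| 0 | 0 | 5.0% | 0% |
| 0.1 | 0.354 | 6.4% | 20% |
| 0.2 | 0.707 | 10.9% | 40% |
| 0.3 | 1.061 | 18.6% | 60% |

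Because the test is two-sided, these probabilities do not depend on which arm the bias favours.

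**The case against.** **The sentence may only mean randomization.** Section 4.1 speaks of unbiased assignment and of mitigating confounding, so 2.1 could be read as loose praise of a randomized design. No test or decision rule in 4.5 depends on it, and the Discussion already warns about self-report. This explains the wording but does not rescue it. The sentence promises attribution specifically to the intervention, and balanced baselines do not deliver that for self-rated scales.

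**The testers.** A reader might infer that outcome assessors are unblinded. The documents do not support this. Section 4.3 lists tests and time points, but not who runs them or what they know. A condensed article can leave that to the full protocol. All that can be said is that the article describes no blinding of testers. The conclusion for self-rated outcomes holds either way.

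**Certainty about the arm.** A reader might also infer that every participant will know their arm. That too goes beyond the text. Section 2.2 does not say that participants are told which arm is the test arm, and some controls may receive an exercise recommendation. Inferring the arm is easy and likely, but not documented as certain.

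**Size and direction.** The range of 0.1 to 0.3 SD has no source in the article, and the direction is a plausible expectation, not a derived result. Section 4.2 gives a 4-week intervention while 4.3 places the first assessment at 6 months, so how much expectation would persist is unknown. These objections stand, and the figures are illustrative only.

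**The performance tests.** Masked testers would not settle the matter. Walking, sit-to-stand and cognitive tests also depend on the effort of participants who can infer their arm. They measure cognition and physical function, so they cannot corroborate a difference in anxiety, sleep or quality of life. This stands and limits what the second part of the fix can achieve.

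**Conclusion.** The attribution claim in 2.1 is wrong as written for the self-rated outcomes, including anxiety, sleep and quality of life. This follows from three features stated in the article: recognisably different care, prior disclosure of aims and methods, and self-rating. No fuller document could make participants blind to the kind of care they receive. For the performance tests the article leaves the position open, and no defect is shown.

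If the bias were 0.1 to 0.3 SD, the false-positive rate at 25 per arm would rise from 5% to about 6% to 19%. That range rests entirely on the assumed bias. The trial can proceed, but the sentence limits what can honestly be concluded and should be corrected.

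**What to change.** 1. **Section 2.1.** Replace the attribution sentence with a statement that participants are not blinded, that differences in self-rated outcomes may include expectation effects, and that such differences cannot be attributed specifically to the AI prescription.
2. **Section 4.3.** Confirm that MoCA and MMSE, Rey-O, line orientation, SPPB, the 400 m walk and the 30 s sit-to-stand are run from a fixed script by staff without access to allocation. If this is not already planned, adopt it where existing staffing allows. It has to be settled before the 6-month assessments, because masking cannot be recovered afterwards. It reduces tester bias in those tests only.

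The first change costs wording and a less favourable claim. The second costs a line of text and, if new, some scheduling inconvenience for 50 participants. The article gives no staffing details, so feasibility is for the sponsor to judge.

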**Figure 1 fig1:**
[figure not shown]
Overview of study design incorporating AI model development and randomized controlled trial phases.

### Recruitment

2.2

Participants for the study will be recruited from the general community and the Department of Mental Health at Guangdong Second Provincial General Hospital, utilizing platforms like WeChat or other social media to effectively reach and engage potential participants. To reach a diverse pool of potential participants, advertisements will be placed in community centers and local newspapers in Guangzhou. At the Department of Mental Health, individuals receiving care will have the opportunity to consent to the use of their medical records for research purposes and express their interest in participating in research studies. Prospective participants will initially undergo a telephone screening process to determine their eligibility. This screening will include an evaluation based on predefined inclusion and exclusion criteria, alongside the Physical Activity Readiness Questionnaire for Everyone (PAR-Q Plus) (29), a widely recognized tool for assessing an individual’s readiness for physical exercise. Upon passing the initial screening, eligible participants will be invited to a detailed consent and screening session. This session, which can be conducted either over the phone or in person, will provide comprehensive information about the study, including its objectives, methodology, potential risks, and benefits. During this session, research staff will ensure that participants fully understand the study and are comfortable with their involvement, thereby upholding the highest standards of ethical research practice. For participants involved in the AI part of data collection, we are offering a subsidy of 100 RMB per person. This incentive is designed to encourage their active participation and consistent engagement with the data collection process. Additionally, for participants in the RCT, we are providing a more substantial subsidy of 300 RMB per person.

### Time frame

2.3

The enrollment of participants for this study will commenced on January 1, 2024. This will mark the beginning of a crucial phase in our research, where we started gathering data from a diverse group of individuals, crucial for the development and testing of our AI model. The final assessment of the study is anticipated to be completed by January 1, 2027. This assessment will mark the conclusion of the two-year follow-up period post the trial completion.

### Inclusion criteria

2.4

In this study, participants are selected based on specific inclusion criteria to ensure both relevance and safety. Individuals aged 18 to 65, diagnosed with a mental illness such as depression, anxiety disorders, bipolar disorder, or schizophrenia, are eligible. They must be in a stable medical condition, with no acute mental health crises in the past 6 months, and have the cognitive ability to understand and consent to the study procedures. Physical capability for exercise, assessed by the PAR-Q Plus, is required, alongside a willingness to adhere to the study’s protocol. Participants should not be engaged in any other structured exercise program, have access to communication tools for remote monitoring, and reside within a distance from the study site in the Guangzhou area. These criteria are designed to ensure that participants are representative of the target population and can safely and effectively engage in the study.

### Exclusion criteria

2.5

Certain exclusion criteria are established to maintain the integrity and safety of the research. Individuals are excluded if they are under 18 or over 65 years of age, to focus the study on a specific adult demographic. Those without a clinically confirmed diagnosis of mental illness, or those experiencing acute mental health crises or hospitalizations within the last 6 months, are also excluded. Participants with severe cognitive impairments that prevent understanding of the study or informed consent, as well as those with physical conditions or disabilities that contraindicate exercise, based on the PAR-Q Plus assessment, are not eligible. Additionally, individuals already engaged in a structured exercise program or unable to commit to the study’s schedule and protocols are excluded. Further, lack of access to necessary communication tools for remote monitoring or residing outside the practical geographical scope of the study (beyond the Guangzhou area) also leads to exclusion. These criteria ensure that participants are well-suited to the study’s aims and methods while safeguarding their well-being.

### Data entry

2.6

Throughout the data collection process, no personal identifiers will be gathered to ensure participant confidentiality. All data collected on paper will be securely stored in locked cabinets, accessible only to authorized study personnel. Trained staff will be responsible for entering alphanumeric data, implementing range checks to verify the accuracy of data values. Both alphanumeric data and neuroimaging files will be stored on a secure server managed by UBC, adhering to strict data protection protocols. To further safeguard participant privacy, all collected data will undergo a de-identification process, removing any potential links to individual identities.

## Machine learning model development

3

### Model inputs

3.1

In our study, a range of comprehensive assessment tools have been meticulously chosen to serve as inputs for the machine learning model (shown in Table 1). These include the State and Trait Anxiety Inventory (STAI), Center for Epidemiologic Studies Depression Scale (CES-D), Pittsburgh Sleep Quality Index (PSQI), and several others, each uniquely contributing to a multi-dimensional understanding of participant well-being. The collected data from these tools encompass various aspects of mental health, physical activity, social engagement, and general well-being. For instance, the STAI provides insights into anxiety levels, the CES-D focuses on symptoms of depression, while the PSQI assesses sleep quality. Other questionnaires like the CHAMPS Physical Activity Questionnaire and the Lubben Social Network Scale offer valuable data on physical activity habits and social network strengths, respectively. This diverse dataset is fed into the machine learning model to analyze patterns, correlations, and potential predictors of mental health outcomes.

**Table 1 tab1:** Comprehensive assessment tools utilized as input for machine learning model.

Questionnaires	Description
Mindfulness attention awareness scale (MAAS) (36)	This 12-item questionnaire focuses on assessing mindfulness during daily activities like conversation, commuting, and eating, underlining the importance of mental presence in everyday life
CHAMPS physical activity questionnaire for older adults (37)	A specialized 41-item questionnaire that gauges the weekly frequency and duration of physical activities particularly relevant to older adults
Sedentary behavior questionnaire (SBQ) (38)	This questionnaire specifically measures the time spent in nine different sedentary behaviors during a typical weekday and weekend, highlighting patterns of physical inactivity
Lubben social network scale – revised (LSNS-R) (39)	A 12-item questionnaire evaluating social engagement with family and friends, crucial for understanding social support networks
Social provisions scale (SPS) (40)	A 24-item scale that measures the availability and adequacy of social support in an individual’s life
UCLA Loneliness scale (41)	A 20-item scale focused on assessing feelings of loneliness and social isolation, reflecting on the emotional aspects of social health
Health care resource utilization (HRU) (42)	A 10-item questionnaire that asks participants about their health care visits, services used, and their ability to perform chores, aimed at calculating the economic burden of health care needs
State and trait anxiety inventory (STAI) (43)	This comprehensive 40-item questionnaire evaluates mood and levels of anxiety, providing valuable insights into the psychological well-being of participants
Center for epidemiologic studies depression scale (44)	A detailed 20-item questionnaire designed to measure symptoms associated with depression, focusing on experiences over the past week
Pittsburgh sleep quality index (PSQI) (45)	An in-depth 19-item questionnaire that assesses sleep quality over the previous month. It employs subjective ratings across seven different components, including sleep quality, latency, duration, habitual efficiency, disturbances, use of sleeping medication, and daytime dysfunction
STOP bang questionnaire (46)	An 8-item tool aimed at assessing the risk of obstructive sleep apnea, crucial for understanding sleep-related health risks
Life space questionnaire (47)	A 6-item questionnaire that measures the mobility extent of older adults, providing insights into their functional range and independence
Everyday memory questionnaire (EMQ) (48)	A comprehensive 28-item questionnaire that evaluates memory failures occurring in the past 3 months, offering a window into cognitive health

